### Interventional group 2 (sleep only)

Participants randomized to the sleep-only group will participate in an 8-week intervention utilizing the Elemind Neuromodulation headband, an electroencephalography-based, non-invasive, wearable device designed to reduce onset latency through personalized acoustic stimulation that is tailored to the unique brainwaves of each individual (see Fig. 1). This arm is intended to assess the efficacy of a home-based neuromodulation strategy in older adults with varying cognitive and functional baselines.

**Fig. 1 Fig1:**
[figure not shown]
Elemind Neuromodulation Headband. The wearable Elemind Neuromodulation headband (left) promotes a reduction in sleep onset latency through acoustic stimulation based on each individual’s unique brainwaves (left). The Elemind Neuromodulation headband can be utilized in conjunction with machine learning approaches to optimize personalized treatments. The user-programmed device will use Bluetooth low energy or a direct USB-C connection (right) to control the device and transfer data obtained by the headband to the Elemind application on a smartphone, which will collect sleep metrics

#### Device use and sleep monitoring

Subjects will start with a 7-day onboarding-screening period, during which participants will wear the Elemind Neuromodulation headband nightly without stimulation to passively establish a baseline sleep pattern and to ensure initial eligibility criteria are satisfied. Following this, the neuromodulation feature will be activated, and participants will be instructed to wear the device at least 3–4 nights per week for 8 weeks. Each use will deliver bone-conduction-based acoustic stimulation tailored to the participant’s real-time brainwave activity. The headband will collect continuous data on multiple sleep metrics, including total sleep time, sleep efficiency, sleep onset latency, restlessness, and time spent in various sleep stages (light (N1/N2), N3, REM). Sleep data will be delivered to the Elemind smartphone application. Raw data will be reviewed regularly for artifacts, such as signal dropout and excessive motion. Nights with incomplete data (e.g., < 4 hours of recording or ≥ 10% missing epochs) will be flagged and excluded from analysis and will prompt follow-up instructions and/or re-onboarding support. The Elemind Neuromodulation device’s sleep staging outputs, while designed to approximate polysomnographic benchmarks, are considered proxies and will be interpreted accordingly. In addition, participants will wear the Lys device continuously throughout the 8-week trial period. The Lys device will measure the intensity, color, and duration of light exposure to gain insights into the relationship between light, sleep, circadian cycles, and energy levels. This device works by communicating with the company’s proprietary app, named Insight, to display light exposure data to the user as well as to provide the individual with goals and insights related to light and health. Additionally, Lys communicates with a separate app, called Collect, which will be used by the researchers to download data at the conclusion of the study. In addition, subjects in this group will also receive Fitbit devices and will be asked to wear the device continuously to passively gauge physical activity levels throughout the trial duration.

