The intervention will span 8 weeks and will follow structured phases, including screening, baseline assessment, intervention, and follow-up. Full Digital Neuro-Signature Platform augmented reality cognitive assessments will be used to assess cognition at baseline and week 8 (post-intervention) as well as biweekly as brief pulse assessments throughout the trial duration. Blood-based biomarkers will be collected via venipuncture at Quest Diagnostics at baseline and post-intervention under standardized fasting conditions. Specifically, in order to maximize participant safety and minimize any potential influences of acute exercise [20], the pre-intervention blood draws will be obtained no sooner than 24 hours and no later than seven (7) days before the initiation of the first exercise session, and post-intervention blood draws will be obtained within 24–48 hours after completion of the final exercise session. No blood draws will occur on the same day as in-lab exercise. Data from digital devices will be temporally synchronized using structured protocols to support integrated analysis, and raw sleep data will be reviewed for artifacts, with re-instruction provided for invalid nights. Patient-Reported Outcomes Measurement Information System (PROMIS) surveys [21] and validated physical activity questionnaires (including the Physical Activity Scale for the Elderly (PASE [22]) and the Community Healthy Activities Model Program for Seniors (CHAMPS [23])) will be administered via REDCap at baseline (week 0) and at week 8 during the in-person visits. The CASE study is designed to assess adherence, detect early efficacy signals, and explore behavioral mechanisms that may prevent or delay AD through modifiable lifestyle-based behavior interventions.

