Individuals meeting these pre-screening criteria will then be scheduled for an in-person screening visit to provide written informed consent and further assess eligibility criteria via a 7-day screening period. After signatures are obtained, each prospective subject will be provided with a copy of the signed informed consent document. All procedures have been approved by the University of Miami Institutional Review Board (IRB) requirements and federal privacy protections and will be conducted in accordance with the Helsinki Declaration. Thereafter, prospective participants will be randomized into one of three arms and will receive intervention-specific, wearable devices and will be instructed on how to use these devices. All prospective participants will receive Fitbit devices, while those assigned to sleep or sleep + exercise intervention will receive an Elemind Neuromodulation headband to be used daily without stimulation during the initial 7-day screening period and a Lys device. Prospective participants in all groups will be asked to wear the Fitbit device continuously to establish baseline physical activity levels and to confirm sedentary to lightly active physical activity levels in order to satisfy eligibility criteria for those assigned to interventions that involve exercise, and those assigned to the sleep-only or sleep + exercise interventions will be asked to wear the Elemind Neuromodulation headband without stimulation while the device actively collects sleep data for seven consecutive nights to establish baseline sleep patterns, ensure comprehension of and comfortability with wearing the headband; additionally, this will confirm subquality sleep pre-intervention to satisfy eligibility criteria for those assigned to groups that involve the sleep intervention.

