#### Baseline and follow-up visits

Data will be collected at baseline, biweekly, and at the 8-week follow-up to assess changes in sleep, exercise, biomarkers, and cognition. After consent and randomization, participants will be onboarded in person to each intervention-specific device and observed for a 7-day period prior to the baseline visit to establish baseline sleep patterns and/or physical activity levels relevant for each assigned intervention and to ensure all eligibility criteria are satisfied. Cognitive function will be measured using an augmented reality-based tool at baseline and week 8, with brief pulse assessments administered twice-weekly throughout the intervening period. Blood biomarkers will be collected via venipuncture at Quest Diagnostics (baseline and week 8). Physical activity and sleep data will be respectively monitored using Fitbit (all groups) and the Elemind headband (sleep and sleep + exercise groups), and light exposure will be tracked via the Lys device (sleep and sleep + exercise groups). Participants will also complete validated self-report surveys (e.g., PASE, CHAMPS–MET, PROMIS instruments) to capture psychosocial and behavioral variables at weeks 0 and 8. This multimodal approach will enable temporally-aligned, comprehensive data capture across digital and self-reported domains (see Table 3).

**Table 3 Tab3:** Timeline of questionnaires provided

Variable	Screening	Baseline	8-week
Basic Info Screening Form (eligibility criteria)	X		
Physical Activity Readiness Questionnaire (PAR-Q)	X		
Quick Mild Cognitive Impairment screen (QMCI), 6-item	X		
Demographic Questionnaire		X	
Chronic Health Questionnaire		X	X
PROMIS Self-reported Cognitive Functioning Behaviors Short Form		X	X
PROMIS Sleep Disturbance 4a		X	X
PROMIS Emotional Support 4a short form		X	X
PROMIS Depression 4a shot form		X	X
PROMIS Anxiety 4a short form		X	X
PROMIS Social Isolation 4a		X	X
General PROMIS Life Satisfaction 5a		X	
Cross Ethnic-Racial Identity Scale		X	
PASE Physical Activity Questionnaire (exercise and sleep + exercise interventions only)		X	X
CHAMPS-MET Physical Activity Questionnaire (exercise and sleep + exercise interventions only)		X	X

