#### Protocol structure and considerations

To reduce participant burden and improve standardization, in-lab exercise sessions and cognitive assessments will follow the same cadence and structure as in the exercise-only arm: twice-weekly, 60-minute, supervised sessions that will focus on aerobic and resistance training, home-based walking program, and brief digital cognitive assessments (the Digital Neuro-Signature Platform) immediately after each session. Participants will also wear the Elemind Neuromodulation headband for at least 3–4 nights per week across the 8-week period, with an initial 7-day, passive, onboarding screening phase of wearing the headband nightly without stimulation in combination with wearing the Fitbit device continuously to establish baseline sleep patterns, physical activity levels, and ensure that all eligibility criteria are satisfied. Finally, subjects will also wear the Lys device continuously throughout the 8-week trial period.

To manage cumulative burden, scheduling flexibility will be emphasized. Although participants will be offered a choice of days and times for in-lab sessions to fit each participant’s weekly routines, morning times will be strongly encouraged across all participants, as prior work has suggested that older adults generally show better cognitive and exercise performance in the mornings [42, 43]; this will further improve standardization. Staff will work closely with participants to accommodate visit times and ensure ample time for recovery between activities. Weekly adherence and well-being check-ins will be conducted and documented to monitor fatigue, motivation, and adverse effects.

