Clinically, this study fills a critical gap by targeting a middle-aged and aging population who have greater cognitive vulnerability to AD. The trial moves beyond self-reported behaviors to integrate real-time, ecologically valid assessments of physical activity, sleep, and cognitive function. In addition, the use of the Digital Neuro-Signature Platform, an innovative Food and Drug Administration Breakthrough Device that deploys augmented reality to evaluate cognitive performance in realistic virtual tasks, marks a significant methodological advancement. The augmented reality-based digital cognitive and functional assessment’s ability to simulate real-world scenarios in order to test higher-order cognitive performance, such as memory, navigation, and object placement, offers a nuanced and sensitive measure of cognitive function that surpasses traditional pencil-and-paper tests, especially for detecting early, subtle impairments [64, 66].

Moreover, the study will incorporate light exposure, which will be captured via the Lys device, as a covariate and potential effect modifier. Light is a critical zeitgeber that regulates circadian rhythms, thereby influencing sleep quality and exercise levels [67, 68]. By capturing ambient light exposure, this study will be able to utilize an improved modeling approach to more robustly test how environmental context modulates interventional efficacy and contributes to individual variability in response. This multidimensional measurement strategy will enhance the rigor and ecological validity of the study, essentially intersecting cognitive neuroscience, digital health, and precision prevention.

From a public health perspective, this trial reflects an innovative shift toward digitally enabled, lifestyle-based interventions for cognitive, brain, and cardiometabolic health. Although the exercise intervention utilized in this trial will be conducted in-person to ensure standardization of procedures, the findings may nonetheless inform future hybridized models of care delivery. The inclusion of wearable sensors (Fitbit and Lys) and neuromodulation technology (Elemind) embodies a next-generation toolkit for behavioral clinical trials. These tools will allow for fine-grained, longitudinal monitoring of physiological, behavioral, and cognitive data with minimal participant burden—an essential consideration for older adults, particularly those with cognitive impairment.

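### No pre-intervention light value is planned, so the proposed effect-modifier analysis would rest on light measured during treatment

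*Protocol article*

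**What the plan says.** Light exposure enters the protocol article in three roles. *Objectives* lists it as the fourth objective, a possible modulator of sleep. *Analysis plan* places it among the tertiary outcomes. The *Discussion* goes further: light is to be a covariate and possible effect modifier, used to "test how environmental context modulates interventional efficacy and contributes to individual variability in response".

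The wear instructions are these:

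- *Interventional group 2, Device use and sleep monitoring*: "participants will wear the Lys device continuously throughout the 8-week trial period".
- *Interventional group 3, Protocol structure and considerations*: "subjects will also wear the Lys device continuously throughout the 8-week trial period".
- *Screening and consent*: participants in the two headband arms "will receive an Elemind Neuromodulation headband to be used daily without stimulation during the initial 7-day screening period and a Lys device". The wear instructions that follow for those 7 days name the Fitbit and the headband, not the light sensor.
- *Baseline and follow-up visits*: "participants will be onboarded in person to each intervention-specific device and observed for a 7-day period prior to the baseline visit", the purpose being "to establish baseline sleep patterns and/or physical activity levels relevant for each assigned intervention". Light is not mentioned.

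*Study design overview* separates the phases: "The intervention will span 8 weeks and will follow structured phases, including screening, baseline assessment, intervention, and follow-up". The device sections for the Fitbit and the headband each describe a 7-day collection step before the intervention and a second step during it. The section on the Lys device describes no such first step.

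**The concern.** An effect modifier or adjustment covariate should be fixed before the treatment can act on it. If light is known only from the treated weeks, a light-by-intervention interaction mixes two things: people who live in brighter or darker surroundings responding differently, and the intervention changing how much light people get. Adjusting for such a variable can also remove part of the effect being estimated.

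The protocol itself describes ways in which light could change once the intervention starts. The Insight app shows participants their light data and gives them light goals. The combined arm adds two supervised site sessions a week, with mornings strongly encouraged, and walking on the other five days. The sleep-only arm has neither the sessions nor the walking.

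The lack of a light value for the unstimulated week also means that change in light cannot be set beside change in sleep. The omission cannot be repaired once stimulation has begun.

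**Working it through.** The point rests on no power, alpha or sample-size figure, so the check sets the statements side by side and counts what is planned.

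**1. Planned windows for each wearable**

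| Device | 7-day onboarding | 8-week intervention |
|---|---|---|
| Fitbit | stated, all arms | stated, all arms |
| Headband | stated, nightly without stimulation, two arms | stated, at least 3–4 nights a week, two arms |
| Lys | issued, no wear stated | stated, continuous, two arms |

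Two of the three wearables have an explicit baseline window. The third has a stated window that begins later. In the combined-arm section, the 7-day phase is described as headband together with Fitbit, and the Lys is then added for the 8 weeks.

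**2. Who has light data**

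Two arms of 20 receive the Lys: 2 × 20 = 40 of 60 participants, or 67%. The number with a specified pre-intervention light value is 0 of 60.

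**3. Nights that pair light with headband sleep**

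- Onboarding: 7 headband nights without stimulation. Planned light wear: none stated. Planned pairs: 0 of 7.
- Intervention: at least 3 × 8 = 24 to 4 × 8 = 32 headband nights, all within the light-wear window. Required pairs: about 24 to 32.

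*Device use and sleep monitoring* says that after onboarding each use of the headband delivers stimulation. Every planned pair is therefore a stimulated night, and the only planned unstimulated headband nights have no planned light.

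**4. Which comparison could use light as a modifier**

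The exercise-only arm has no Lys, and both Lys arms receive stimulation. The only between-arm comparison with light on both sides is combined versus sleep-only, that is, the addition of exercise. This is also the comparison in which site sessions and walking differ by arm, so on-treatment light is least safe as a modifier or covariate there.

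**5. The protocol's own practice elsewhere**

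For the amyloid and tau markers, *Biomarker collection strategy* uses baseline values as covariates or effect moderators. A pre-intervention light value would follow the same standard.

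**The case against.** The strongest reply is that the protocol never says light goes unrecorded in the onboarding week. The sensor is issued at the start of it, participants are onboarded to every intervention-specific device before it, and the Fitbit is likewise described in one place as worn throughout the 8-week trial, yet it is clearly worn at baseline. Wear instructions for a tertiary sensor may also sit in the full protocol. This stands in part: 0 of 7 is planned coverage, not certain coverage, and some participants may wear the sensor anyway. But the Fitbit has a separate, explicit 7-day step and the Lys has none. Uneven, uninstructed wear would not supply a usable baseline.

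A reader might infer that the fourth objective fails without baseline light. The documents do not support that. The objective asks whether light modulates sleep, no analysis of change in light is proposed, and *Temporal synchronization* plans time-stamped, aligned light and sleep streams. Concurrent association over 8 weeks remains possible.

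A reader might also take 56 days of continuous light wear as the amount of usable paired data. It is not: headband use of at least 3–4 nights a week limits the required pairs to about 24 to 32.

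It can further be said that the effect-modifier use appears only in the *Discussion*, that the *Analysis plan* specifies no light-by-intervention model, and that light is tertiary in a hypothesis-generating pilot. All of this is correct and keeps the severity low. It does not make on-treatment light suitable for the use the *Discussion* gives it.

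Finally, baseline wear is not free of side effects. App goals could alter light behaviour, and possibly sleep, in the very week that sets baseline sleep and decides eligibility or reassignment. This objection stands, and the remedy has to deal with it.

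**Conclusion.** The concern holds in a limited form. No pre-intervention light value is planned for any of the 40 participants due to receive the sensor, and the covariate and effect-modifier use in the *Discussion* would rest on light measured while treatment, app goals and arm-specific activity can change it. The fourth objective loses the unstimulated light–sleep relation and any comparison of change with change, but it is not defeated.

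The conclusion assumes that the wear period given for the Lys means the 8 intervention weeks, as the phase structure in *Study design overview* and the two-step descriptions for the other devices suggest. That treatment would shift light is plausible from the protocol's own description, but the documents give no figure for its size. Onboarding follows assignment in *Screening and consent*, so light from that week would be pre-intervention but not pre-randomization. It would still precede stimulation and exercise.

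Severity is low. No primary or secondary analysis in the *Analysis plan* depends on light.

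**What to change.** State in *Screening and consent* and in both headband-arm sections that participants wear the already issued Lys during the 7-day onboarding week, with Insight goals and feedback withheld for that week so that baseline sleep and eligibility are not disturbed. Apply the same to anyone reassigned to the sleep-only arm who undergoes a second onboarding week.

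Use mean light over the onboarding week as the modifier and covariate, restricted to the two Lys arms. Describe light during the intervention as a concurrent association with sleep.

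If baseline wear is declined, say so and remove the effect-modification wording from the *Discussion*.

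The cost is one more week of sensor wear, one added instruction and withholding app feedback for 7 days. No additional device is needed for those already assigned to a headband arm. The protocol does not say whether the sensor can record with Insight feedback switched off, so that should be confirmed first.

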#### Cognitive pulse assessments

Full-length, digital cognitive assessments (approximately 20 minutes) will be conducted at week 0 and week 8 in a quiet testing room at the University of Miami or, if unable to complete in person, via a secure video conference with a trained research assistant or postdoctoral fellow. Throughout the study duration, participants in this group will also complete brief, twice-weekly cognitive pulse assessments in each participant's  own home setting using the Digital Neuro-Signature Platform cognitive tool on two mornings per week after wearing the Elemind Neuromodulation headband the night before.

#### Biomarker collection strategy

Similar to the first arm, cardiometabolic and brain health will also be assessed using a hybrid biospecimen collection protocol in this arm. Specifically, two venipuncture-based blood draws will be conducted through Quest Diagnostics, occurring during week 0 (pre-intervention) and week 8 (post-intervention) after the final utilization of the Elemind Neuromodulation headband has been completed. Samples will be assessed for hs-CRP and HbA1c levels as well as fasting total cholesterol, HDL, LDL, triglycerides, insulin, and C-peptide levels, which will provide time-sensitive insight into the inflammatory, glycemic, lipid, and insulin resistance markers across the intervention period. Changes in neuroaxonal stress and overall neurodegeneration from baseline will be assessed via plasma NfL levels at weeks 0 and 8. Furthermore, AD-linked neuropathology will be assessed at baseline only via plasma samples, including Aß1–42, Aß1–40, Aß1–42/Aß1–40 ratio, and p-tau217.

